### In- and exclusion criteria

Inclusion criteria:Aged between 18 and 70 years of ageHave the capability of standing and exercising

Exclusion criteria:Not be working for the full duration of the first study year (i.e. retirement, maternity leave)Very high physical activity level: more than 30 min/day in prolonged bouts (≥10 min) moderate to vigorous physical activity. This exclusion criteria will be checked by analyzing accelerometer data. Note that because subproject 1 has shown that almost all office-workers reported high levels of sedentary behavior [17], sedentary behavior will not be used as an exclusion criterion. Data collected of these persons will be excluded from the analytical sample

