#### Motivational counselling

This motivational counselling has a comparable design but a different focus in either intervention, respectively aiming at physical activity or sedentary behaviour. The counselling will be performed by professional health coaches from a health promotion company Itrim who will receive additional training on CBT techniques and on physical activity and sedentary behavior. These training sessions will last for two days and will be held by CBT educated psychologists and physical activity expert. All Itrim coaches have experience with behavior counselling and are used to face-to-face meetings with clients. In total there will be five sessions; three individual and two group sessions. The first individual session is scheduled to last 60 min, the other individual sessions 45 min, and group sessions 90 min. In between session one and two there will be two weeks and thereafter sessions are 4–5 weeks apart. After session three (in the middle of the active intervention period, approximate 3 months) the participants will be equipped with accelerometers and inclinometers to be worn for 7-days. At session four the participants will receive feedback of their physical activity or sedentary behavior (dependent on which group they are in) based on the assigned intervention. To standardize counselling sessions, coaches will get a checklist with multiple issues that they should address during the session and selected sessions will be recorded. The CBT techniques include 1) Goal setting tied to values and identifying the individual’s resources and boundaries for making behavior changes, 2) Functional analysis including antecedents and consequences of unwanted and wanted behavior, and 3) Acceptance techniques. The active components in the counselling according to the taxonomy of behavior change [20] is described in detail in Additional file 1.

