#### Waiting list

The waiting list control will be a passive control group that will be measured again after 6 months. After this measurement they will start the assigned randomized intervention.

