This 24- months study includes 5 measurement time points, with measurements every 6 months. The 5th measurement point will only be performed provided that drop-out rate is not higher than 30% and sufficient resources are available [69]. When persons drop-out of the study they will be asked whether they are still willing to wear the accelerometers and/or fill out a short version of the questionnaire including only the main distal outcomes.

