### Statistical analyses

In accordance with the research questions, statistical analyses will be conducted to determine whether the groups differ in changes over time in proximal, distal as well as secondary outcomes. Statistical significance will be set at the 5% level (two-tailed). To adjust for company and clustering, analyses will be performed using multilevel modelling. The models will include allocated group (reference group = control group) and baseline values. Both crude models and models adjusted for potential confounders will be determined. Potential confounders will be defined a priori based on the findings from the larger research project. Separate models will be made for the different outcomes regarding physical activity, sedentary behavior, mental health and cognition. All analyses will be performed using both per protocol and intention to treat approaches, were intention to treat is defined as persons attending at least 3 out of 5 counselling sessions.

Moderator analysis will examine whether intervention effects differ across individual (e.g. age, gender and education). Mediator analyses will test whether individual and organizational factors, described under working mechanisms, mediated the intervention effects.

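### Intention to treat is defined as attending 3 of 5 counselling sessions: an adherence rule that can select only within the active arms, so no valid ITT set is defined

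*Protocol article*

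**What the plan says.** The Statistical analyses section of the protocol article states: "All analyses will be performed using both per protocol and intention to treat approaches". It goes on: "were intention to treat is defined as persons attending at least 3 out of 5 counselling sessions". No other definition of intention to treat appears in the document. The per-protocol set is not defined, and neither approach is named as primary.

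The Motivational counselling section describes what is counted: "In total there will be five sessions; three individual and two group sessions". The counselling is part of both active interventions: "This motivational counselling has a comparable design but a different focus in either intervention".

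The Waiting list section describes the comparator: "The waiting list control will be a passive control group that will be measured again after 6 months". Of what comes next it says: "After this measurement they will start the assigned randomized intervention".

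The Design section bases the trial's outcomes on the first two measurement points, and the primary hypothesis (Research questions section) compares the interventions with the waiting list at 6 months. The Randomization section places randomisation after the first data collection. The Sample size section says of people who drop out that "they will be asked whether they are still willing to wear the accelerometers", or complete a shortened questionnaire, or both.

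**The concern.** Intention to treat keeps everyone in the arm to which they were allocated, so that the groups differ only by chance and by the intervention. A threshold on sessions attended does the opposite: it chooses people on something that happens after allocation and that probably depends on motivation, workload, stress and health. These are close to the outcomes of this trial.

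The selection is also one-sided, because the comparator has no sessions to attend before the endpoint. A result reported under the ITT label would be read as protected by randomisation when it is not. The trial's stated aim is effectiveness, which makes this the analysis readers will look for first.

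**Working it through.** **Step 1. Set the sections side by side.**

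| Element | Where | What follows |
|---|---|---|
| Randomisation follows baseline | Randomization | Attendance is a post-randomisation variable |
| Counselling belongs to the two active interventions | Interventions; Motivational counselling | Only the active arms can have an attendance count by 6 months |
| Controls passive until the 6-month measurement | Waiting list | Every control has zero sessions at the endpoint |
| Outcomes rest on baseline and 6 months | Design | Controls' later counselling falls outside the randomised comparison |
| Control is the model's reference group | Statistical analyses | Controls must stay in, so the rule cannot be meant for them |

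The only workable reading is that active-arm participants with 0, 1 or 2 sessions are removed and the remaining attenders are compared with all controls.

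**Step 2. Consequence for data already sought.** An active-arm participant who leaves before a third session may still be asked to wear the devices or answer the short questionnaire. Under the rule those data would not enter the set labelled ITT.

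**Step 3. Check against the sample size.** The Sample size section allows for loss of clusters and for 20% unavailable data (missing data and individual drop-outs). It mentions no attendance filter, so exclusions under the rule would come on top.

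**Step 4. Illustrate the size.** No stated figure is in dispute. The document gives the SD of sedentary time (1.4 h/day) and the target difference (1 h/day). The rest is assumed: a share q of the active arm below three sessions (0.20–0.30), a correlation r between attendance propensity and outcome (0.3–0.5), normal variables, and no true effect.

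Without baseline adjustment: bias in SD = r × φ(z_q) / (1 − q), where φ is the standard normal density and z_q the normal quantile at q.

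- q = 0.20: φ(z_q)/(1 − q) = 0.280/0.80 = 0.350
- q = 0.30: φ(z_q)/(1 − q) = 0.348/0.70 = 0.497

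| q | r | Bias (SD) | × 1.4 h/day |
|---|---|---|---|
| 0.20 | 0.3 | 0.105 | 0.15 |
| 0.20 | 0.5 | 0.175 | 0.25 |
| 0.30 | 0.3 | 0.149 | 0.21 |
| 0.30 | 0.5 | 0.248 | 0.35 |

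Weaker assumptions (10–40% below three sessions, r from 0.1 to 0.3) give 0.02–0.19 SD with the same formula.

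**Step 5. Allow for the planned baseline term.** Assume a baseline-to-6-month correlation ρ of 0.6. To a first approximation:

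- If attendance relates equally to the baseline and 6-month values, the bias is multiplied by 1 − ρ = 0.40: 0.105 × 0.40 = 0.04 up to 0.248 × 0.40 = 0.10 SD.
- If attendance relates to baseline only through the 6-month value, it is multiplied by 1 − ρ² = 0.64: 0.105 × 0.64 = 0.07 up to 0.248 × 0.64 = 0.16 SD.

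Together this is roughly 0.04–0.16 SD, or 0.06–0.22 h/day. A smaller ρ raises these figures and a larger one lowers them.

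**The case against.** The best defence is that the sentence is a slip. Three of five sessions is an ordinary per-protocol threshold. If the labels were exchanged, the other analysis would be the full allocated set and the plan would be sound. That is quite possible. It does not rescue the text, because nothing elsewhere corrects it, and exchanging the labels would leave the true ITT set still undefined. Nor is this a detail that an article leaves to a fuller plan: the article states the definition and states it wrongly.

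Baseline adjustment is a fair second point. It shrinks the illustrated bias but does not remove it, and it helps less where attendance is tied to change rather than to level.

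Several stronger readings are tempting but not supported:

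- *That the rule empties the control arm.* The model uses control as its reference group, so this cannot be intended.
- *That both analyses, or the main one, rest on compliers, so the trial has no unbiased estimate.* Per protocol is undefined and neither approach is ranked. The document supports only that no valid ITT set is defined.
- *That all drop-out data are lost.* Controls who drop out, and active participants who leave after the third session, are untouched by the rule.
- *That the eligibility criteria add a second post-randomisation exclusion.* The criterion "Not be working for the full duration of the first study year" gives foreseeable examples and can be judged at enrolment. The later sentence about excluding data most naturally refers to highly active people identified from the accelerometer.

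**Conclusion.** The definition is wrong as written. A post-randomisation adherence rule carries the ITT label, it can operate only in the two active arms before the 6-month endpoint, and the document offers no valid ITT set in its place. This conclusion follows from the text and needs no assumption about attendance.

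The size of any bias is illustrative. Under the assumptions in the working it is about 0.10–0.25 SD unadjusted, where the largest case is about a third of the 1 h/day target for sitting, and roughly 0.04–0.16 SD with baseline adjustment. The direction depends on who attends: if healthier or more motivated people do, the intervention is flattered; if those most in need do, it is penalised.

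**What to change.** Replace the definition. Intention to treat should mean all eligible participants in randomised clusters, analysed in the arm to which their cluster was allocated, regardless of sessions attended, with all available 6-month data including those from people who dropped out. Name this as the primary analysis.

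Use the 3-of-5 rule to define a supportive per-protocol set for the active arms, and state how controls enter that set.

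The change is to wording and needs no new data. Its cost is some dilution compared with attenders only. As an upper bound, suppose attenders gain the planned 1 h/day, and the 20–30% below three sessions gain nothing. The allocated-arm difference is then 0.8–0.7 h/day (1 × 0.8 to 1 × 0.7). Actual dilution may be smaller, because low attenders are still exposed to the environmental and organisational components.

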### Research questions

For inactive and sedentary office workers, does a multi-component intervention to promote physical activity or reduce sedentary behavior lead to more favorable physical activity and sedentary behavior?Do favorable changes in physical activity or sedentary behavior result in better mental health and cognition, on the short and long term?

The primary hypothesis is that the multi-component interventions will favorably change office-workers physical activity or sedentary behavior as compared to the waiting list control group at 6 months. The secondary hypothesis is that these changes in physical activity patterns will in turn have positive longer term effects on mental health and cognition.

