#### Working mechanisms

##### Blood analyses

Participants will be instructed to fast for at least eight hours preceding the assessment. Fasting venous blood samples will be obtained from the antecubital vein. Per measurement point, two blood samples (each 5 mL) will be drawn. Cooled (~ 4 °C) samples will be centrifuged to aquire plasma and serum, aliquoted and stored at minus 80 °C. HbA1c will be analyzed using the IFCC method [44]. Plasma and serum levels of inflammatory markers, BDNF [45, 46], VEGF [46], and IGF-1 [46] will be analyzed using enzyme-linked immunosorbent assays following manufacturer’s instructions. Furthermore, genetic profiling of BDNF genes of will be performed [47, 48]. Genomic DNA will be isolated from peripheral white blood cells using the PureGene kit (Gentra Systems, Minneapolis, MN). The Val66Met polymorphism at the BDNF locus will be genotyped using the amplification conditions reported by [49] and detection by fluorescence polarization as described by Chen et al. (1999) [50].

Questionnaires:Exercise self-efficacy [51–53], and comparable questionnaire adjusted for sedentary behaviorFor individual barriers [17] and motivation to change a questionnaire was developed based on previous qualitative research [54–56]Feasibility and acceptability of interventions (self-developed questionnaire)Self-regulation [57]Over commitment [58]Work/non-work interference and enhancement [59, 60]Job Demand-control-support [61]Job insecurity [62]Work engagement [63]Work climate [64]Health-promoting leadership [65]

Additionally, a qualitative study will be performed on feasibility and acceptability of the interventions. For quality control of the counselling intervention sessions will be recorded.

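### Research question 2 asks whether changed activity or sitting improves mental health and cognition, but the mediators named for analysis do not include measured activity or sitting

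*Protocol article*

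**What the plan says.** All references are to the protocol article.

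- **Research questions.** The second question reads: "Do favorable changes in physical activity or sedentary behavior result in better mental health and cognition, on the short and long term". The secondary hypothesis expects that "these changes in physical activity patterns will in turn have positive longer term effects on mental health and cognition". Both make behaviour change the causal step.
- **Statistical analyses, main models.** The section presents its analyses as serving the questions the trial set itself: "statistical analyses will be conducted to determine whether the groups differ in changes over time in proximal, distal as well as secondary outcomes". On content: "The models will include allocated group (reference group = control group) and baseline values". Activity, sitting, mental health and cognition are each modelled separately, in crude and confounder-adjusted form.
- **Statistical analyses, further analyses.** Moderation is examined by individual characteristics such as age, gender and education. On mediation: "Mediator analyses will test whether individual and organizational factors, described under working mechanisms, mediated the intervention effects".
- **Working mechanisms.** The list holds blood analyses and questionnaires on, among others, self-efficacy, barriers and motivation, self-regulation, job demands, work climate and leadership. Accelerometer activity and activPAL sitting are described elsewhere, as proximal outcomes.
- **Interventions and Waiting list.** Each active arm receives five CBT-based counselling sessions. On their content: "The CBT techniques include 1) Goal setting tied to values", followed by functional analysis and acceptance techniques. The control arm is passive until it has been measured again at 6 months.

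**The concern.** The trial's end goal is a pathway: the intervention changes behaviour, and the changed behaviour improves mental health and cognition. The stated analyses cover the first step (group differences in activity and sitting) and the overall result (group differences in distal outcomes). They do not cover the link between the two.

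This would matter less if the interventions could act on the distal outcomes only through activity or sitting. They need not. Counselling that works on values, barriers and acceptance could plausibly change stress or mood with no change in activity, and the control arm has nothing comparable before the 6-month measurement. A gain over control on a distal outcome is therefore open to more than one explanation, and the second research question asks which explanation holds.

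**Working it through.** No stated figure is disputed. The check sets the question beside the analyses and then shows what a group contrast can and cannot identify.

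**1. Question against analysis**

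| Link in the causal chain | Stated analysis |
|---|---|
| Assignment → activity, sitting | Group contrast on proximal outcomes |
| Assignment → mental health, cognition | Group contrast on distal outcomes |
| Working mechanisms as mediators of intervention effects | Mediator analyses |
| Change in activity or sitting → mental health, cognition | None named |

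The last row is the second research question. The models contain group and baseline values, plus confounders in the adjusted version. None is said to contain change in activity or sitting as a term for a distal outcome.

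**2. What the group contrast identifies**

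Let *a* be the effect of assignment on sitting, *b* the effect on Stroop time per hour less sitting, and *c′* the effect of assignment on Stroop by any other route, such as counselling. Then

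total effect = *c′* + *a* × *b*.

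The Sample size section supplies *a* = 1 h/day and a total of 7 s. Three illustrative splits:

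- no effect through sitting: *c′* = 7, *b* = 0, total 7 + 1 × 0 = 7 s;
- half and half: *c′* = 3.5, *b* = 3.5, total 3.5 + 1 × 3.5 = 7 s;
- all through sitting: *c′* = 0, *b* = 7, total 0 + 1 × 7 = 7 s.

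A model with group and baseline value estimates only the total, so the three cases look the same to it.

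**3. Illustration by simulation**

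Assumptions: 41 per group (the article's figure before the design effect), individual randomisation, sitting SD 1.4 h/day, Stroop SD 9.85 s, two-sided alpha 0.05/3 = 0.0167, 4,000 runs.

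- The group contrast was significant in about 79% of runs with no effect through sitting, and in about 80% with all of it through sitting.
- A test of *b*, given group, rejected in about 2% and 100% of runs respectively.

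The first line is the relevant one. The second is idealised: it has no clustering and no mediator-outcome confounding. In the all-through-sitting case, sitting also carries almost all the outcome variation (7 × 1.4 = 9.8 s against an SD of 9.85 s). It shows that the two cases are distinguishable in principle. It is not an estimate of the power of a real mediation analysis.

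**The case against.** The strongest reply is that the group comparisons on distal outcomes answer the article's stated aim, the effectiveness of the multi-component interventions, with randomised evidence. The mediator sentence also does not say that only working mechanisms will be tested, and a condensed article may leave more to an analysis plan.

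The first part stands. The group contrasts are a necessary first step for the second research question, so a reader who inferred that the question goes wholly unaddressed would be going too far. The second part stands only in part. The article does not leave the mediators open: it names a set and ties it to a listed section. An analysis plan that followed this text would test self-efficacy or work climate as mediators, but not the behaviours named in the question. How the cohort phase after 6 months is to be analysed can fairly be left to another document and is not counted here.

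Four stronger readings are tempting and not supported:

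- *Counselling effects will be credited to activity.* The article states no attribution rule, and it describes the interventions openly as including counselling. The wording of the secondary hypothesis creates a risk of misattribution, no more.
- *The BDNF genotype will be tested as a mediator.* It appears among the blood analyses under Working mechanisms, but the mediator sentence speaks of individual and organizational factors, and nothing says that the genotype is one of them.
- *The sample size assumes that cognition changes only through sitting.* The sitting and Stroop inputs are separate calculations, and the article asserts no path between them. They support no statement about power for an indirect effect.
- *Comparing the two active arms would isolate counselling.* The arms differ in behavioural target, gym access and meeting format, and both may change activity.

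**Conclusion.** The concern holds as a mismatch between the second research question and the mediators named to serve it. Followed as written, the plan shows whether assignment changes behaviour and whether it changes mental health and cognition. It does not test whether the one produced the other. The point rests on the text and on the shared counselling component with a passive control, not on any assumed effect size. It has no numerical size: the share of a distal effect that passes through behaviour could lie anywhere from none to all without altering the planned contrasts.

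The randomised comparisons are unaffected. A reader might infer that conclusions on the second research question should rest on the indirect effect alone. That goes too far, because it would displace randomised evidence with an estimate open to unmeasured confounding between mediator and outcome. The change is worth making and is not a fatal flaw.

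**What to change.** In Statistical analyses:

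1. Name accelerometer MVPA and activPAL sitting, each adjusted for its baseline value, as mediators of the intervention effects on the main mental health and cognition outcomes.
2. Report direct and indirect effects for each active arm against control, with intervals that allow for clustering. With 24 clusters planned, 8 per arm, a simple resampling of clusters rests on few units, so the interval method should suit that number.
3. Label the analysis as assuming no unmeasured mediator-outcome confounding. Where mediator and outcome are both taken at 6 months, label it also as assuming their time order. The mid-intervention device wear is described as part of the counselling, so it does not supply an earlier mediator value in the control arm. After 6 months the waiting list starts its own intervention, so later measurements do not restore a randomised time order.
4. Keep the randomised group contrasts as the main evidence on distal outcomes. State that behaviour change caused a distal gain only where the mediation result supports it.

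The cost is one further analysis on data already being collected, with assumptions that the trial cannot verify and must state.
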